#### Clinician Participants

All clinicians from all participating practices will be invited to participate. The clinician sample size will be pragmatic and guided by the study objectives, given the outcomes being measured.

### Intervention

#### Intervention Development

THRIVE was developed through an iterative design process, drawing on principles of co-design [58,59], contemporary behavior change theory, preventive care guidelines, persuasive system design, and principles from nudge theory [60]. In alignment with evidence highlighting the value of motivational communication and self-monitoring [42,43,61,62], nudge design-based principles, such as timely prompts, simplified decision pathways, concise feedback, and guideline-aligned options, are embedded.

Meaningful engagement with community members occurred throughout development. This iterative consultation shaped the platform’s functionality, content clarity, user pathways, notification timing, and overall usability. These refinements aimed to enhance engagement, reduce respondent burden, and ensure that behavioral prompts and decision pathways were intuitive and fit for users’ real-world needs. All consumer-facing content is intentionally designed to be practical and easy to follow, written at a year 7 reading level to maximize comprehension and accessibility [63]. THRIVE is currently only available in the English language. Establishing technical feasibility, core functionality, acceptability, and engagement is important before multilingual versions are developed.

The intervention’s theoretical foundation incorporates the transtheoretical model [64] and the health action process approach [65] to support goal-setting, self-efficacy, and sustained behavior change across different stages of readiness. Preventive action plans and educational content are aligned with contemporary Australian clinical guidelines, including the Royal Australian College of General Practitioners Red Book [66], Cancer Council [67], National Heart Foundation [68], and Kidney Health Australia [69] guidelines. THRIVE follows a continuous update policy, in which content is revised promptly in response to updates to national guidelines or new evidence. All changes are documented using structured version control procedures (Multimedia Appendix 1 [66,68-91]).

THRIVE generates personalized lifetime chronic condition risk estimates using a composite lifetime modeling framework. This model synthesizes demographic variables, behavioral risk factors, family history, anthropometric measures, and selected clinical data based on evidence from Australian and international epidemiological studies. Inputs and effect sizes are derived from hazard ratios, attributable risk fractions, and pooled effect estimates from meta-analyses and high-quality cohort data. Construct validation has been undertaken for risk estimates that have existing short-term (typically 5-year-risk) calculators by benchmarking THRIVE-generated risk scores against these tools, including the Australian Type 2 Diabetes Risk Assessment Tool [70], the Australian Cardiovascular Risk Score [71], and STOP-BANG for sleep apnea [92]. Validation analyses demonstrated moderate (STOP-BANG) to near-perfect (Australian Type 2 Diabetes Risk Assessment Tool) construct alignment with these established tools, and all recommendations are consistent with Australian clinical guidelines [66-69] (Multimedia Appendix 1 [66,68-91]).

Findings from this study, including quantitative engagement metrics and qualitative acceptability data, will inform subsequent model refinement to enhance usability in practice, ensure clinical appropriateness, and integrate into clinical workflows before a future large-scale trial.

#### Intervention Content and User Experience

THRIVE guides users through lifetime chronic condition risk assessments, facilitates goal setting, and tracks and reinforces progress through behavioral “nudges.” The intervention is largely automated and can be used independently by consumers. Once consumer participants have provided consent and completed the preintervention survey, they receive a personalized email link providing access to the THRIVE platform. The online assessment guides users through a dynamic, user-friendly series of questions tailored to individual responses. Questions incorporate 130 validated risk and protective factors, and participants receive real-time feedback to maintain motivation and minimize attrition.

After completing the assessment, participants access a personalized dashboard that presents lifetime risk estimates for 23 chronic conditions, including cardiovascular disease, metabolic conditions, osteoporosis, sleep apnea, various cancers, eye and kidney disease, and an estimated “medical age.” The medical age score reflects the impact of lifestyle choices on microlife calculations (a microlife is a statistical unit representing 30 minutes of life expectancy gained or lost due to daily habits). Color-coded indicators highlight key contributors to risk. These risk estimates and the medical age-metric personalize lifetime risk estimates. Risk estimates and the “medical age” metric are not diagnostic tools and are intended solely for promoting health education and engagement. Multimedia Appendix 1 [66,68-91] provides a summary of all variables included in THRIVE’s risk-modeling framework, as well as the guideline sources informing action-plan content.

The platform translates risk estimates into actionable guidance using rule-based logic aligned with Australian clinical guidelines [66-69]. After viewing their dashboard, participants can access an automated action plan that provides tailored lifestyle and medical screening recommendations aligned with current Australian guidelines. Recommendations are presented using nudge-informed design principles that simplify decision-making while preserving user autonomy.

Consumers can also access a clinician report that consolidates risk estimates, key health indicators, and recommendations, which they can choose to share with their general practitioner or general practice nurse to facilitate preventive-care discussions. This report also identifies Medicare Benefits Schedule items that the consumer may be eligible to receive to promote access to care. However, clinicians retain full discretion regarding consumer eligibility and the appropriateness of any care activity and associated Medicare Benefits Schedule claims.

Consumers are encouraged to set health goals and may choose to integrate data from wearable devices. They can also complete a quarterly “pulse check,” a brief reassessment that updates their health data, provides refreshed risk calculations, and tailors action plans. To support ongoing engagement, participants retain continuous access to their dashboard and can revisit it at any time to review progress or modify goals. Optional behavioral prompts and reminders are delivered to further support sustained use. Figure 1 illustrates the THRIVE dashboard and platform overview.

**Figure 1. F1:**
[figure not shown]
THRIVE dashboard image and platform overview. THRIVE: Tailored Health Risk Insights for Vital Empowerment.

#### Integration With General Practice Workflow

As a prototype, THRIVE currently operates as an externally hosted digital platform that is not integrated into electronic medical record (EMR) systems. To align with clinical workflows, patients access study information through QR codes in the waiting room, enabling them to complete the risk assessment before, during, or between appointments. Clinicians will still retain the ability to refer consumers whom they feel may benefit.

As a consumer-facing intervention, THRIVE empowers consumers to share their study involvement with clinicians through the clinician report, should they wish to prompt discussion about preventive care. Behavioral nudges are provided directly to consumers by THRIVE, without the need for clinician input. This direct link to consumers seeks to support general practitioner and general practice nurse workflows by providing health education, personalized recommendations, and ongoing encouragement.

Through the provision of tailored health information and health promotion education directly to consumers, THRIVE aims to improve the efficiency of preventive care delivery, thus supporting general practitioner and general practice nurse workflows. This feasibility phase will explore how consumers and clinicians prefer THRIVE to interface with general practice, and the findings will inform future co-design and staged EMR integration.

### Data Collection

#### Overview

The recruitment period will span approximately 3 months, with follow-up data collection and analysis concluding around 9 months from the start of recruitment. Data will be collected from consumer and clinician participants across multiple time points. A mixed methods approach will be used, with qualitative insights complementing and adding depth to quantitative data (Figure 2).

**Figure 2. F2:**
[figure not shown]
ePREVENT-360 study flowchart. CHAI: Consumer Health Activation Index; THRIVE: Tailored Health Risk Insights for Vital Empowerment; UTAUT2: extended unified theory of acceptance and use of technology 2.

#### Consumer Data Collection

Quantitative data will be collected via self-administered online surveys at baseline and 6 months post enrollment. These surveys will assess outcomes related to acceptability, engagement, and early indicators of effectiveness, including activation and self-rated health. The estimated total time commitment for consumer participants is 75 minutes over 6 months, including participation in surveys, digital assessments, and optional interviews.

Engagement data will be passively collected through the THRIVE platform, including metrics such as login frequency, dashboard views, goal setting, action plan access, and responses to health reminder prompts. Following the postintervention survey, participants will be invited to opt-in to subsequent interviews by providing their contact details. As part of this process, participants will self-report their level of intervention engagement (eg, high, medium, low, or none), to guide sampling stratification. This process ensures that codified (controlled) and identifiable (protected) data are handled separately.

Approximately 18 to 20 consumer interviews (up to 4 per clinic) will be conducted via videoconference, audio-recorded, transcribed verbatim, and complemented by researcher field notes. A qualitative descriptive approach will be used to explore perceptions of intervention acceptability, sustainability, impact, and opportunities for improvement. Final numbers will be guided by data sufficiency. The semistructured interview guide is included in Multimedia Appendix 1 [66,68-91].

#### Clinician Data Collection

Preintervention and postintervention clinicians will be invited to participate in semistructured interviews. These interviews will explore key feasibility domains such as acceptability, sustainability, perceived impact, and optimization strategies. Approximately 8 to 10 clinicians (2 per practice) will be interviewed via videoconference, with sampling guided by saturation. Interviews will be guided by qualitative descriptive methodology. Interview guides are included in Multimedia Appendix 1 [66,68-91]. The time commitment for clinicians will range from 10 to 40 minutes, depending on their level of participation across survey and interview components.

Clinicians will also complete a postintervention survey. The survey includes 15 items rated on a 7-point Likert scale and captures data on intervention acceptability, perceived usefulness, and ease of implementation, impact on workflow, barriers, and summary of use.

### Outcomes

#### Overview of Outcome Measures

The primary focus of this study is feasibility, which will be assessed through consumer and clinician engagement, acceptability, and perceived sustainability (Table 1). A secondary outcome is preliminary effectiveness, evaluated through changes in consumer activation, self-rated health, and disease risk scores.

**Table 1. T1:** Overview of outcome measures.

Outcome and components	Data collection tool	Participants	Collection timeframe
Primary outcome (feasibility)			
Engagement	Usage logs from THRIVE platform	Consumers	Observation period
Acceptability	UTAUT2^a^ survey questions [93-95]	Consumers and clinicians	Postintervention
Sustainability	Semistructured interviews	Consumers and clinicians	Postintervention
Secondary outcomes (effectiveness)			
Consumer activation	CHAI^b^ survey questions [96]	Consumers	Preintervention and postintervention
Self-rated health	Single-item Likert Scale survey question	Consumers	Preintervention and postintervention
Calculated disease risk scores	AUSDRISK^c^ [70] and AusCVDRisk^d^ [71] scores calculated from THRIVE data	Consumers	Observation period

a UTAUT2: extended unified theory of acceptance and use of technology 2.

b CHAI: Consumer Health Activation Index.

c AUSDRISK: The Australian Diabetes Risk Score.

d AusCVDRisk: The Australian Cardiovascular Disease Risk Score.

The consumer baseline survey will also capture factors that may influence engagement with the intervention, including sociodemographic characteristics, perceived disease threat, and trust in the therapeutic relationship. Perceived disease threat will be measured using 4 validated items from the UTAUT2 framework [93], rated on a 7-point Likert scale ranging from “strongly disagree” to “strongly agree” (⍺=0.817). Trust in the therapeutic relationship will be assessed using the Trust in Physician Short-Form Scale [97]. These baseline variables will form the a priori covariate set for exploratory quantitative analyses examining predictors of engagement with the THRIVE intervention and potential signals of change in secondary outcomes. They will also be used to inform question refinement for the postintervention interviews, ensuring representation of diverse experiences and perspectives across engagement levels.

#### Engagement

Engagement will be measured using THRIVE usage logs, which automatically record participants’ interactions with the platform. Based on these behaviors over the 6-month study period, participants will be classified into 1 of 5 engagement levels (Figure 2). Individuals who consent but do not initiate or complete the risk assessment will be classified within the “no use” engagement category. This group will be included in follow-up surveys and purposive qualitative sampling to capture barriers to engagement.

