### Sample Size

#### Consumer Participants

As a feasibility study, this trial is not powered to detect statistically significant differences in outcomes. Instead, the sample size was determined to allow for the estimation of key feasibility indicators with acceptable precision [52]. If approximately 50% of participants who consent complete the THRIVE health assessment, with a 10% margin of error at a 95% CI, a minimum sample size of 187 consumers will be required.

In line with previous general practice research [53-57], a cluster adjustment was applied to the sample calculation using an intracluster correlation coefficient of 0.05 [53-57]. With an anticipated 5 participating practices and a design effect of 1.95, allowing for an estimated 15% dropout rate, the adjusted sample size requirement will be 215 consumers. Therefore, each practice is expected to recruit at least 43 participants.

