#### Primary Outcome Analyses (Feasibility End Points)

Descriptive statistics will be calculated for all variables, including frequencies for categorical data and means or medians for continuous variables. Engagement levels will be examined in relation to participant characteristics using nonparametric methods, including the Kruskal-Wallis *H* test and the Spearman rank correlation. Acceptability scores will be summarized for each domain of the UTAUT2 [49,98] and compared between user subgroups.

The proportion and patterns of missing baseline and follow-up data will be documented as part of the feasibility assessment. Given the descriptive nature of feasibility end points, no imputation will be undertaken. For baseline acceptability data, incomplete responses will be excluded from domain-level mean score calculations using listwise deletion [105]. Missing usage log data will be interpreted as nonengagement rather than missingness.

As a secondary exploratory analysis, multilevel logistic regression models will be used to examine predictors of engagement, with practice included as a random intercept to account for clustering.

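### The no-use level merges consenters who were never sent the THRIVE link with people who had access and did not use it

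*Protocol article*

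**What the plan says.** Access has a gate. Under Intervention Content and User Experience: "Once consumer participants have provided consent and completed the preintervention survey, they receive a personalized email link providing access to the THRIVE platform".

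The classification rule has no matching condition. Under Engagement: "Individuals who consent but do not initiate or complete the risk assessment will be classified within the" no-use level. The same section sends this group to the follow-up surveys and to purposive interviews about barriers.

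The data source and the missing-data rule point the same way. Engagement comes from the platform: "Engagement will be measured using THRIVE usage logs, which automatically record participants’ interactions with the platform". Under Primary Outcome Analyses: "Missing usage log data will be interpreted as nonengagement rather than missingness".

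The sample size section also counts from consent: "If approximately 50% of participants who consent complete the THRIVE health assessment, with a 10% margin of error at a 95% CI". Engagement is part of the primary outcome: "The primary focus of this study is feasibility, which will be assessed through consumer and clinician engagement, acceptability, and perceived sustainability".

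The Acceptability section gives nonusers their own 12 items. Table 2 declares a barrier to use when the mean score exceeds 4 and at least 70% of participants meet that threshold.

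**The concern.** A consenter who does not finish the baseline survey has no usage log because no link was sent. The stated rules give that person the same code as someone who received the link and ignored it. The two groups say different things. The first reflects the burden of the research procedures, the second the appeal or usability of THRIVE.

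The distinction matters for the decision the study is meant to inform. The Progression Criteria section directs refinements to the intervention, to implementation strategies or to study procedures, and a merged no-use level cannot show which of these is failing. The nonuser barrier items could also be put to people who never saw the product.

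Some loss between consent and link is plausible. The recruitment section lists registration of interest, study information and the consent form on the page behind the QR code, but does not mention the survey there. The survey carries sociodemographic items, perceived disease threat, trust in the physician, the activation index and self-rated health.

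**Working it through.** **The plan's own figure.** Inputs from the sample size section: proportion 50%, margin 10 points, 95% confidence, design effect 1.95, dropout 15%.
- n0 = 1.96² × 0.5 × 0.5 / 0.10² = 96.04
- 96.04 × 1.95 = 187.3 (stated 187)
- 187 × 1.15 = 215.05 (stated 215)

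The figures reproduce, so this point does not rest on an arithmetic error. The 50% applies to consenters: "If approximately 50% of participants who consent complete the THRIVE health assessment".

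**Path of a consenter who stops at the survey.**
1. Consent given, survey incomplete: the condition for sending the link is not met.
2. No link, so the assessment cannot be started.
3. Assessment not started: no-use under the Engagement rule.
4. No log: nonengagement under the missing-data rule.
5. No-use: included in the follow-up survey and in sampling for interviews on barriers.

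No visible step separates this person from a link recipient who did nothing.

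**Size.** Let s be the share of consenters who do not finish the survey. The article does not give it, so 5% to 30% is assumed. Hold the plan's 50% per consenter fixed. Then:
- never sent the link, out of 215 = 215 × s
- completion among link recipients = 0.50 / (1 − s)
- share of the no-use level never sent the link = s / 0.50

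| s (assumed) | Never sent, of 215 | Completion among link recipients | Share of no-use never sent |
|---|---|---|---|
| 0% | 0 | 50.0% | 0% |
| 5% | 10.8 | 52.6% | 10% |
| 10% | 21.5 | 55.6% | 20% |
| 15% | 32.2 | 58.8% | 30% |
| 20% | 43.0 | 62.5% | 40% |
| 30% | 64.5 | 71.4% | 60% |

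**Barrier indicator.** Suppose exactly 70% of responding link recipients meet the barrier threshold, and a share w of nonuser respondents were never sent the link. The pooled proportion then lies between 0.70(1 − w) and 0.70(1 − w) + w. For w = 10% that is 63% to 73%; for w = 20%, 56% to 76%. The merged group can cross the 70% line in either direction. These are outer bounds. People who abandoned the first survey may seldom answer the six-month one, so w among respondents may be well below the last column of the table.

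**The case against.** The strongest reply is that the plan is consistent about its denominator. Both the sample size section and the Engagement section start from consent, and completion per consenter is a legitimate measure of the whole pathway. That stands.

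A reader might infer that the engagement estimate is biased downward, with a true 50% reported as 45%, 40% or 35% when 10%, 20% or 30% do not finish the survey. The document does not support this. Those figures move the 50% from consenters to link recipients, whereas the plan's 50% already absorbs any loss at the survey. An estimate is not biased for differing from another quantity. No visible numeric engagement cutoff would be crossed either: the stated thresholds concern acceptability, and progression is judged flexibly alongside the interviews.

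Three further replies have partial force.
- Figure 2, which holds the five engagement levels and the flowchart, is not shown and may separate these people. That limits confidence, but the visible wording does not separate them.
- The plan will document missing baseline data, and interviews with the no-use group could bring out survey burden. That gives a count and some context, but does not change how these people are coded or who enters the barrier analysis.
- Flow-table detail belongs in the SAP. That would answer a mere omission, but here the article itself fixes the classification and the reading of absent logs.

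**Conclusion.** The point holds as a fault in classification. On the visible text, the no-use level and the nonuser barrier analysis may include people who were never offered THRIVE. The per-consenter completion proportion is sound as defined, and replacing it would be a matter of choice.

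The size is unknown. With 50% completion per consenter and assumed survey noncompletion of 5% to 30%, completion among link recipients would be 52.6% to 71.4%, and 10% to 60% of the no-use level would never have had access. If consent and survey are done in one sitting, the effect is negligible.

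The conclusion assumes that the link is withheld until the survey is complete. This is inferred from the stated order of steps, as the article does not say what happens to those who stop partway. It also assumes that Figure 2 does not already separate them.

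**What to change.** In the SAP:
- Keep completion per consenter as the whole-pathway indicator, and report completion per link recipient beside it.
- Split no-use into link not sent (survey incomplete) and link sent, not used.
- Limit the reading of absent logs as nonengagement to people who were sent the link.
- Restrict the nonuser barrier indicator in Table 2 to link recipients.
- Report the funnel: consented, survey complete and link sent, assessment started, assessment completed.

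If Figure 2 already makes the split, align the Engagement wording with it.

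The only extra item needed is whether and when each link was sent. The cost is one more row in the flow table and a slightly smaller nonuser group. The Data Analysis section has the SAP preregistered before data extraction, and the Results section reports 25 consents by 17 April 2026 with collection continuing, so the change may still be prespecified.
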